# Efficacy of endometrial receptivity testing for recurrent implantation failure in patients with euploid embryo transfers: study protocol for a randomized controlled trial

**DOI:** 10.1186/s13063-024-08125-6

**Published:** 2024-05-28

**Keywords:** Endometrial receptivity testing, Recurrent implantation failure, Personalized embryo transfer, Randomized controlled trial, Live birth

## Abstract

**Background:**

Embryo implantation remains a critical barrier in assisted reproductive technologies. One of the main causes of unsuccessful embryo implantation is window of implantation (WOI) displacement, particularly in patients with recurrent implantation failure (RIF). Therefore, a reliable diagnostic tool for identifying the optimal WOI is essential. Previous data has suggested that a novel RNA-Seq-based endometrial receptivity testing (ERT) can diagnose WOI, guide personalized embryo transfer (pET), and improve pregnancy outcomes in patients with RIF compared to standard embryo transfer (sET). However, there is still a lack of evidence from randomized controlled trials (RCT) with sufficient power to determine whether pET based on ERT can increase the rate of live births as the primary outcome.

**Methods:**

This trial is a prospective, single-blind, parallel-group RCT (1:1 ratio of pET versus sET). Infertile women with RIF who intend to undergo frozen-thawed embryo transfer (FET) after preimplantation genetic testing for aneuploidy (PGT-A) with the availability of at least one euploid blastocyst for transfer will be enrolled and assigned into two parallel groups randomly. Participants in the intervention group will undergo ERT and then pET based on the results of ERT, while those in the control group will undergo sET. The primary outcome is live birth rate.

**Discussion:**

The findings of this study will provide evidence for the effect of pET guided by ERT on pregnancy outcomes in patients with RIF.

**Trial registration:**

Chinese Clinical Trial Registry ChiCTR2100049041. Registered on 20 July 2021.

**Supplementary Information:**

The online version contains supplementary material available at 10.1186/s13063-024-08125-6.

## Background

Infertility is regarded as a major public health concern, affecting 1 in 6 couples of reproductive age globally [1]. Since first introduced in 1978, in vitro fertilization (IVF) has brought hope and great benefits to millions of infertile couples. Currently, IVF is widely used all around the world, with more than 2,000,000 cycles being performed every year [2, 3].

Despite the substantial advancements in assisted reproductive technologies (ART), implantation remains a critical barrier in IVF [4]. More than 50% of IVF cycles still fail due to implantation failure [5]. Recurrent implantation failure (RIF) refers to the failure of implantation following repeated embryo transfer cycles, which is commonly encountered among IVF patients. RIF poses a significant challenge to clinicians and also causes great distress to infertile patients. Given the emotional and financial burden that comes with RIF, numerous interventions have been proposed to investigate and overcome this condition, while very few have proven effective [6].

Successful implantation requires a competent embryo, a receptive endometrium, and a synchronized dialog between the embryo and the endometrium [7]. Endometrial receptivity is a prerequisite for embryo implantation [8], and decreased endometrial receptivity accounts for up to two-thirds of implantation failure [9]. Endometrial receptivity occurs in a self-limited period during the mid-secretory phase, known as window of implantation (WOI). WOI typically falls between days 19 and 23 of the menstrual cycle [10] or on day 5 following progesterone treatment (P + 5) in a hormone replacement cycle [11]. However, the timing and duration of WOI are not identical for every woman. WOI displacement has been reported in about 25 to 50% of RIF patients and may be one of the main causes of implantation failure [12, 13]. Therefore, identification of the optimal WOI can help guide personalized embryo transfer (pET) and restore synchronicity between the embryo and the endometrium, which could potentially serve as a therapeutic approach to improve reproductive outcomes for patients with RIF.

Historically, Noyes et al. established histological criteria to “date” the endometrium [14], which has been used for decades, while being questioned regarding its accuracy, objectivity, and reproducibility [15, 16]. Despite the research that has been devoted to defining WOI through biomarkers and molecular indicators, reliable methods are still lacking in clinical practice [15, 17]. Therefore, valid and accurate methods are needed to identify the WOI and help determine the optimal timing for embryo transfer.

With the breakthroughs in high-throughput omics, transcriptomics has emerged as a promising diagnostic tool for endometrial receptivity. In 2011, a Spanish study first reported a microarray-based technique known as the endometrial receptivity array (ERA), which assesses endometrial receptivity status by analyzing the expression of 238 genes related to endometrial development [18]. Furthermore, in 2018, a research team from China established a novel endometrial receptivity testing (ERT) technology based on whole transcriptome RNA sequencing (RNA-Seq) analysis, combined with a machine learning algorithm, identifying 175 predictive genes [19]. Previous studies have shown that the analysis of gene transcriptomes, compared to histological methods, can more accurately and objectively assess endometrial receptivity and the timing of WOI with reproducible results [20–23].

Yet, the clinical efficacy of these new technologies requires further validation. Recently, there have been several randomized controlled trials (RCTs) evaluating the efficacy of ERA in the general population of IVF [24, 25], whereas no RCT has been conducted with regard to ERT and those with RIF. Notably, the ERT technology is gaining popularity due to the advantages of RNA-Seq, including high sensitivity, dynamic range, accurate quantification, and the ability to perform whole-transcriptome analysis [26]. Therefore, there is an urgent need for well-designed RCT to determine the efficacy of ERT, and whether pET based on ERT would improve pregnancy outcomes in women with RIF.

## Methods/design

### Study objective

This study aims to evaluate whether personalized embryo transfer (pET) based on ERT improves live birth rate compared with standard embryo transfer (sET) in patients with RIF.

### Design and setting

This is a prospective, single-blind, parallel-group RCT being performed in the Center for Reproductive Medicine, Ren Ji Hospital, Shanghai Jiao Tong University School of Medicine. The recruitment period will be from August 2021 to June 2024. All eligible patients will be randomly assigned to the intervention arm (pET) or control arm (sET) with a 1:1 ratio. The study design flowchart is shown in Fig. 1.

**Fig. 1 Fig1:**
[figure not shown]
Flowchart of the study design

The study protocol was approved by the ethics committee of Ren Ji Hospital, Shanghai Jiao Tong University School of Medicine (reference number KY2021-081-B). The trial was registered in the Chinese Clinical Trial Registry (http://www.chictr.org.cn/; registration number ChiCTR2100049041). The trial will be conducted and reported in compliance with the Consolidated Standards of Reporting Trials (CONSORT) guidelines issued by the Enhancing Quality and Transparency of Health Research (EQUATOR) network. The study’s procedures will be fully explained to each participant by a research investigator. Each participant is required to sign an informed consent before taking part in the study.

### Eligibility criteria

#### Inclusion criteria

The inclusion criteria are as follows:Women with RIF, which is defined as failure to achieve a clinical pregnancy under one of the following conditions:Three or more embryo transfer cycles, with embryos transferred being of good quality (criteria of good-quality embryos are shown in Table 1)Two or more euploid blastocyst transfer cyclesWomen aged 20–39 years old at the time of autologous oocyte retrievalWomen who intend to undergo frozen-thawed blastocyst transfer (FET) after preimplantation genetic testing for aneuploidy (PGT-A)Women who have at least one good-quality euploid blastocyst for transferWomen who are capable of providing informed consent

**Table 1 Tab1:** Criteria of good-quality embryo

Embryo	Scoring system	Criteria of good quality
Blastocyst (day 5 or day 6)	Gardner	≥ 4BC
Cleavage (day 3)	Puissant	7–10 cell 3; 4 or compact
	Peter	7–10 cell I; II or compact

#### Exclusion criteria

The exclusion criteria are as follows:Women who have been diagnosed with diseases affecting the uterine cavity, including uterine malformation, submucous fibroids, intramural fibroids protruding into the uterine cavity, and untreated hydrosalpinxWomen or their partners with chromosomal abnormalities (not including chromosome polymorphisms)Women with a history of recurrent pregnancy loss, defined as two or more failed pregnancies clinically recognized by ultrasonography or histopathologic examinationWomen with thin endometrium (< 6 mm) before embryo transferWomen with contraindications to endometrial biopsy, pregnancy, or assisted reproductive technology

### Sample size

Previous researches demonstrated that compared to sET, pET guided by ERT could increase pregnancy rates by about 25% in women with RIF [19, 27]. According to the retrospective data of our center, live birth among women with RIF following frozen-thawed euploid embryo transfer is approximately 35%. In the present study, we assume that the live birth rate will be improved from 35% in the sET arm to 60% in the pET arm.

For the sample size estimations, we will use a 2-tailed test with a statistical significance set at *α* = 0.05 and a statistical power of 1 − *β* = 0.80. The ratio between groups will be 1:1. Therefore, we need to include at least 118 women (59 women in each arm). Taking into consideration a dropout rate of 10%, we expect to include a total of 132 enrollees (66 enrollees in each arm).

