### Data analysis plan

The data will be analyzed using SPSS (version 26.0, IBM Corp, Armonk, NY). Normally distributed continuous variables will be presented with mean ± standard deviation (SD), while non-normally distributed continuous variables with median and interquartile ranges (IQR). Independent samples *t*-tests or Wilcoxon’s rank sum test will be used to test the between-group differences as appropriate. Categorical variables will be presented with frequency and percentage. The Pearson chi-square and Fisher’s exact tests will be used to test the between-group differences as appropriate. A two-sided alpha level of 0.05 will be considered statistically significant.

The primary analysis will be conducted according to the intention-to-treat (ITT) principles. The primary outcome, live birth rate, will be compared between the two groups using the Pearson chi-square test. Women lost to follow-up will be considered as not having had a live birth. Secondary outcomes, including rates of biochemical pregnancy, clinical pregnancy, implantation, ongoing pregnancy, and pregnancy loss, will be analyzed using the Pearson chi-square test or Fisher’s exact test as appropriate. Secondarily, a per-protocol analysis will be performed among participants who complied with the trial protocol.

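### The 10% dropout allowance assumes that dropouts leave the analysis, but the primary ITT analysis mostly counts them as no live birth, so power at 66 per arm could be as low as about 75% rather than 80%

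*Protocol article*

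**What the plan says.** All statements are in the protocol article.

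- **Sample size, effect and error rates.** The control rate comes from the centre's own retrospective data: "live birth among women with RIF following frozen-thawed euploid embryo transfer is approximately 35"%. For the trial, "we assume that the live birth rate will be improved from 35% in the sET arm to 60% in the pET arm". The test is two-sided at 0.05, "and a statistical power of 1 − *β* = 0.80", and allocation is equal: "The ratio between groups will be 1:1". No sample size formula is named.
- **Sample size, numbers.** The result is "we need to include at least 118 women (59 women in each arm"). It is then raised for dropout: "Taking into consideration a dropout rate of 10%, we expect to include a total of 132 enrollees (66 enrollees in each arm").
- **Data analysis plan.** The primary analysis follows intention-to-treat principles and compares live birth with the Pearson chi-square test. "Women lost to follow-up will be considered as not having had a live birth".
- **Primary outcome.** The event is a live birth that follows the frozen-thawed euploid blastocyst transfer.
- **Discontinuation criteria.** The reasons for dropping out are spontaneous pregnancy, no viable embryo after thawing, and a request to withdraw.
- **Timing.** Allocation is obtained on the day of the biopsy (Randomization and blinding). The transfer follows in the next menstrual cycle (Frozen-thawed embryo transfer).

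**The concern.** Dividing a sample size by one minus the dropout rate suits an analysis from which dropouts are removed: 66 women are randomised per arm, about 59 are analysed, and those 59 carry the planning rates. The primary analysis here works differently. All randomised women stay in the denominator, and a woman with no observed live birth after the study transfer adds a failure. A failure added in the same proportion to both arms lowers both rates and shrinks their difference, and the extra seven women per arm do not make up for that.

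The 35% does not already contain this loss, because it is described as a rate following transfer. Randomisation comes about a cycle before transfer, so a woman who never reaches transfer is in the ITT denominator but has no counterpart in the 35%.

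At stake is a stated property of the design. The abstract justifies the trial by the lack of adequately powered randomised evidence on live birth. A non-significant result would be read against 80% power, although on the protocol's own dropout figure the chance of missing the assumed effect could be about 25% rather than 20%.

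**Working it through.** **Inputs.** Rates 0.35 and 0.60, two-sided alpha 0.05 (z = 1.960), power 0.80 (z = 0.8416), 1:1 allocation, dropout 10%, 66 per arm (all from Sample size); ITT, the Pearson test and the no-live-birth rule (from Data analysis plan). Equal dropout in the two arms is an assumption.

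**Step 1. Reproduce the plan's figures.** With the unpooled-variance formula,

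n = (1.960 + 0.8416)² × (0.35×0.65 + 0.60×0.40) / 0.25² = 58.7, so 59 per arm.

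Then 59/0.9 = 65.6, so 66 per arm and 132 in total. Both stated figures reproduce exactly.

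**Step 2. Rates when the 10% count as failures.**

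0.9 × 0.35 = 0.315 and 0.9 × 0.60 = 0.540, a difference of 22.5 points instead of 25.

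**Step 3. Power at 66 per arm.** With the pooled null variance, which corresponds to the Pearson test, the mean rate is 0.4275:

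- 2 × 0.4275 × 0.5725 = 0.4895, square root 0.6996
- 0.315×0.685 + 0.540×0.460 = 0.4642, square root 0.6813
- z = (0.225×√66 − 1.960×0.6996) / 0.6813 = (1.828 − 1.371) / 0.6813 = 0.670, so power is 74.9%

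Exact enumeration of the uncorrected Pearson test over two binomials gives 74.2%. With the unpooled formula that reproduces 59, z = 1.828/0.6813 − 1.960 = 0.723, so power is 76.5%. The shortfall therefore does not depend on the choice of formula.

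**Step 4. Smaller shares counted as failures.** The same calculation at 66 analysed per arm:

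| Share counted as no live birth | Expected rates | Power, normal (pooled) | Power, exact Pearson |
|---|---|---|---|
| 0% | 35.0% v 60.0% | 82.8% | 81.8% |
| 2% | 34.3% v 58.8% | 81.3% | 80.3% |
| 5% | 33.25% v 57.0% | 79.0% | 78.0% |
| 8% | 32.2% v 55.2% | 76.5% | 75.7% |
| 10% | 31.5% v 54.0% | 74.9% | 74.2% |

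**Step 5. What would give 80% in the 10% case.** At 66 per arm, the rate among women who do not drop out would have to rise from 35% to 61.6% by the normal approximation. Exact power at 61.6% is 79.2%, and it reaches 80% at about 62%, a difference of about 27 points. For the assumed 35% v 60%, 80% power would take 75 per arm by the pooled formula, or 73 by exact enumeration.

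**The case against.** **The rule names only women lost to follow-up.** The Follow-up protocol section speaks of women who drop out or are lost to follow-up as if these were two groups, and loss to follow-up is not among the listed dropout reasons. A reader might infer that the protocol expressly counts the whole 10% as failures; it does not. For a woman with no viable embryo, or who conceives before transfer, the result follows from ITT together with the outcome definition, since she has no live birth after the study transfer. For a woman who withdraws, it is partly inference. This objection stands, and it is why a range is needed.

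**Enrolment precedes randomisation.** Hormone preparation and biopsy take place in the first cycle after enrolment, and only women with a successful biopsy are randomised. Women lost before that point never enter the ITT set, and for them dividing by 0.9 is the right correction. The phrase about enrollees in each arm points to randomised women, but the text is not decisive. If all losses came before randomisation, 59 per arm would be analysed undiluted, with power of 78.4% (79.2% exact). If they split evenly (63 per arm, 5% diluted), power would be 77.0% (79.1% exact). The 75% is therefore the low end at a 10% loss rate.

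**The formula for 59.** A reader might also infer that 59 is an arithmetic error because the pooled formula for the Pearson test gives 61.4, hence 62. The documents do not support that. No formula is named, 59 is the correct output of a standard one, and exact Pearson power is 79.2% at 59 per arm and 80.3% at 60. There is nothing to correct there.

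**Materiality.** The sample size, test, analysis set and type I error all stay as they are, and the loss is at most about 5 points of power. That bears on the weight of the point. It does not make the stated power correct.

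**Conclusion.** The point holds as a misstatement of power. The dropout inflation and the primary analysis rule rest on different treatments of the same women. If all of the stated 10% are lost after randomisation, equally in both arms, and counted as no live birth, power for 35% v 60% with 66 per arm is about 75% instead of 80%. With 5% so counted it is about 78–79%, and with 2% about 80–81%.

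A flat statement that power is 75% would go too far, because the share of dropouts counted as failures is not fixed by the text. Neither the ITT rule nor the counting of lost women as having no live birth is at fault. What needs correcting is the power attached to 132 women. This is worth fixing but does not threaten the validity of the trial.

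**What to change.** Keep 132 women and leave the analysis unchanged. Restate the Sample size section along these lines:

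> With 66 women randomised per arm and analysed by intention to treat, power to detect 35% v 60% is about 75% if 10% in each arm are counted as having no live birth, about 78–79% if 5% are, and about 80–81% if 2% are. In the 10% case, the difference detectable with 80% power is about 27 points (35% to about 62%).

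The figure of 59 per arm can stand.

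The cost is wording only: no added participants and no look at outcome data. The downside is that the stated power becomes slightly less favourable. As enrolment was still under way when the article was submitted, the change should be made before outcomes are analysed.

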### Randomization and blinding

All eligible women will be randomly assigned to one of two study arms according to a computer-generated dynamic block randomization sequence (sized 2, 4, and 6). The randomization sequence is generated by biostatisticians in the data coordinating center (DCC) using the SAS software version 9.2 (SAS Institute, Cary, NC) and has been input into an online randomization system by the DCC staff members prior to initiation of the study. The sequence will be kept strictly confidential by the DCC staff, thus to ensure that the study investigators are all blinded to the upcoming group allocation. On the day of endometrial biopsy, authorized investigators will log in to the password-protected account to get allocation information for eligible subjects. This is a single-blind clinical trial since it is not feasible to blind the doctors. Group allocation and ERT results will not be disclosed to all study participants.

### Screening

At the screening visit, all participants will be made aware of the trial and study plan. Eligible couples who are interested will sign a written informed consent and complete a comprehensive medical history review, physical examination, and pelvic ultrasound. The history of previous fertility treatments (including ovarian stimulation, oocyte retrievals, embryo transfers, hysteroscopy, and history of chronic endometritis) will be recorded. When necessary, screening for immunological and thrombophilic factors and chronic endometritis will be recommended.

Safety assessment includes but not limited to complete blood count (CBC), liver and renal function, fasting blood glucose, and blood pressure. Figure 2 (SPIRIT diagram) is a schedule of the study process including enrollment, interventions, and assessment. This protocol refers to the SPIRIT Reporting Guidelines [28], and the SPIRIT Checklist is shown in Additional file 1.

**Fig. 2 Fig2:**
[figure not shown]
SPIRIT diagram for the schedule of enrollment, interventions, and assessments

### Endometrial biopsy and endometrial receptivity testing

During the first menstrual cycle after enrollment, the endometrium will be prepared using hormone replacement treatment (HRT) to carry out ERT. Participants will be instructed to take oral estradiol valerate (Progynova, Delpharm Lille SAS) and/or estradiol tablets (Femoston, Abbott Biologicals B.V.) at a dose of 4 to 6 mg daily, starting from the 2nd to the 5th day of the menstrual cycle. The dose of estradiol will be individualized and can be increased to 8 mg daily if endometrial thickness is less than 7 mm after 14 days of administration. When the endometrial thickness is adequate, with serum progesterone level less than 1.5 ng/mL, vaginal progesterone gel (Crinone, Merck Serono) will be initiated within 24 h at a dose of 90 mg daily. Oral dydrogesterone (Duphaston, Abbott) will also be added 10 mg twice daily. The day of the first progesterone administration is defined as P + 0. An endometrial pipelle biopsy will be performed after five consecutive days (120 ± 6 h) of progesterone administration (P + 5). After endometrial pipelle biopsy, progesterone will be administrated for an additional 7 days and then discontinued.

The collected endometrial sample will be placed into 1.5 mL RNA-later buffer immediately for RNA stabilization, sealed, and cryopreserved at − 20 °C for preservation. Endometrial receptivity testing will be carried out within 7 days after sampling. The procedures will include total RNA extraction of endometrial sampling, RNA reverse transcription, library construction and sequencing, and data analysis using a machine learning algorithm. ERT results will be obtained within 15 days. Participants with non-informative results will be recommended to undergo a repeat testing. Any remaining specimens will be responsibly discarded after the endometrial receptivity analysis. No specimens will be retained for future use.

### Intervention

Participants who have a successful endometrial biopsy will be randomized into one of the two arms:A)Intervention arm (pET arm): participants will undergo personalized embryo transfer based on ERT results. Specifically, the transfer will be performed at the standard timing (P + 5) if the ERT result is receptive. For participants with non-receptive results, relative to standard timing, the specific recommended adjustment ranged from 24 to 48 h later for pre-receptive results and 24 to 48 h earlier for post-receptive results, e.g., the transfer will be performed 24 h later (on P + 6) if the result shows 24 h pre-receptive.B)Control arm (sET arm): participants will undergo standard embryo transfer on P + 5.

